**Figure 4 F4:**
[figure not shown]
Data transfer.

##### Website with minimal information

The website available for the control group is limited and contains information about the minimal intervention (i.e. medical prevention consults *without *tailored feedback and *without *reminder from study office). It is also used as a means for study measurements at certain times during the 3-year follow up (Table 1). This limited website contains *general *feedback after the questionnaire with multiple assessments has been filled out by the study participants from the control group. This *general *feedback (= not tailored) is about physical activity, fat intake and smoking and is modified for different measurements in time to avoid drop-out. However, the advice will always be formulated very abstract to avoid 'contamination' of the control group as was the case in another multiple risk factor cardiovascular intervention study[38].

#### Maximal intervention

##### Medical prevention consultation + tailored feedback + reminder from study office

The maximal intervention includes the medical prevention consultation described under the minimal intervention. However, the maximal intervention includes two extra services in relation to the medical prevention consultation.

Firstly, supplementary to the therapeutic goals which are communicated to the patient, the intervention group receives tailored feedback according to the stage of change the study participant is in. For this purpose, the table to for stage of change assessment (Table 2) is included in the EPR. The GP asks for PA and diet which statement fits the participant's situation best. If it is a smoker, the stage of change for quitting smoking is assessed as well. Following this stage determination, the GP gets information about the stage of change the study participant is in for each behaviour, namely: precontemplation, contemplation, preparation, action or consolidation[23]. The tailored feedback that follows is also based on principles from Motivational Interviewing (MI) [39]. Tailored feedback following a classification in the contemplation stage for smoking gives the GP following information: "Accept and talk about the ambivalence of the patient regarding quitting to smoke"; "Talk with the patient about the advantages and disadvantages of smoking and quitting smoking. Don't give arguments to quit smoking yourself"; "Advise the patient to download the quitting to smoke leaflet on the personalised website"; "Advise the patient to look at step 1 and step 2 of the quitting to stop manual on the personalised website". Tailored feedback can be easily printed and given along with the participant by the GP. This printed tailored feedback for the participant following a classification in the contemplation stage for smoking contains following information: "You want to quit smoking and you know it could have advantages, but something keeps you from actually quitting"; "It can be a good idea to think about the advantages and disadvantages of smoking and quitting to smoke. The quitting to smoke manual (step 1 and step 2) on the website can be an aid in this process"; "You can also download a quitting to smoke leaflet". This kind of advice is given to every study participant in the intervention group for all relevant health behaviours.

Secondly, the intervention group receives the supplementary service of being reminded of their next follow-up prevention consult by the study office. As mentioned above, this target date is dependent on the cardiovascular risk of the participant. This reminder will be send by mail or the patient will be reminded by telephone.

##### Personalised Website with tailored feedback

The intervention group gets access to a personalised website with tailored feedback based on questionnaires. Fig 5 shows the site plan of the personalised website. This website is supposed to aid people with behaviour change. The content is based on specific theories on behaviour change, such as the TTM[23,40], Self-Determination Theory (SDT) [30] and Theory of Planned Behaviour (TPB)[26]. Furthermore, operant learning principles (e.g. stimulus control, contingency management), principles from behavioural cognitive therapy (e.g. decisional balances, problem-solving techniques) and relapse prevention techniques are used as a basis for the content of the website, in particular for the manuals [40,41].

**Figure 5 F5:**
[figure not shown]
**Site plan of the personalised website (maximal intervention)**. PA: Physical Activity.

The personalised website contains tailored feedback after the questionnaire with multiple assessments has been filled out by the study participants. This tailored feedback regarding physical activity and fat intake is borrowed from previous research with proven efficacy and completely integrated in the website [11,18]. Moreover, more extensive tailored feedback on other assessment measures (e.g. stage of change, autonomous motivation for PA) is given in the different files on the website (PA file, Food File, Stop smoking File). In the General overview all activity from the patient and results are summarised. The General overview contains several extra's, namely: short links to the PA diary, Food diary and Stop smoking diary; results from medical prevention consultations and a personal calendar with important dates (target date for follow-up medical prevention consultation, start dates for behaviour change). On the homepage and in the Files (Cardio File, PA File, Food File and Stop smoking File) personal messages for each participant can be given. The message could be, for instance, an encouragement for behaviour change, an answer to a question of the participant or an announcement for an initiative of importance for the participant (e.g. group counselling for smoking-cessation). On the forum on the homepage participants can post messages, communicate with each other and ask questions to the PreCardio-team. The PreCardio-team guarantees answers concerning cardiovascular prevention and behaviour change. If the PreCardio-team can't provide an answer, other specialists will be consulted to provide an answer to the study participants. Of course, people can find all contact information of the PreCardio-team (study office) in the section "Contact us".

The PA file contains several PA programmes with different difficulty levels. The easiest programme is "Minimove", this is a programme with mainly tips for improving PA through (Nordic) walking aiming at a health benefit. The programme most in line with the PreCardio mission, namely CVD prevention, is the "Reduce my risk" programme. This programme is a fitness programme aimed at improving physical fitness through more intensive PA. The basis for the fitness programme is a specially developed algorithm linked to the step test used in the study (Fig 6). Three different training programmes are advised, according to step test score determined by physical fitness assessment.

**Figure 6 F6:**
[figure not shown]
Algorithm for fitness programme "Reduce my risk" (maximal intervention).

##### Support from multidisciplinary team

Next to the personalised website with tailored feedback, study participants of the intervention group are entitled to support from a multidisciplinary team. This multidisciplinary team includes: a cardiologist, a general practitioner, a psychologist, a physiotherapist and a dietician. Different media will be available for this personal contact: personal messages on the website, the forum on the website, e-mail, telephone and group sessions. The first types of media will be more frequently used than the latter, dependent on the stage of behaviour change patients are in. Moreover, the cost-effectiveness of the prevention programme must be guarded. The psychologist (= behaviour coach) can aid people more thoroughly with behaviour change, using the different manuals and behavioural (cognitive) therapy.

#### GP intervention

At GP-level a tool for computer-assisted cardiovascular risk screening (EPR) will be implemented. Minimal two information sessions for GPs will be organised in a university building with information about the study and education about the EPR. GPs will have access to an informational website. This informational website contains information about CVD prevention in general with a summary of the latest guidelines (also in a newsletter sent by mail). (Moreover, relevant articles will be provided to the GPs in PDF-format). Furthermore, it contains information about the PreCardio-study and the role of the GP in the study. On this website information about the EPR will be available (installation, how to use, background). GPs are provided with information on behaviour change, including video registrations of motivational interviewing adaptations for PreCardio. In the section on behaviour change more information will be given about the stages of change and type D-personality as a risk factor for CVD. The website for GPs also contains an overview of the personalised website for patients from the intervention group. GPs have access to a forum where they can post messages to open a debate with their participating colleagues about CVD prevention or the PreCardio-study or messages with a question for the PreCardio-team. In other sections contact information and links to relevant websites can be found.

### Analysis and power

A power calculation was performed to determine the number of study participants needed to detect a significant effect of the PreCardio prevention programme. A t-test will be used to compare the means of the outcome measures from the intervention and the control group. The sample size calculation is based on the population standard deviation of the primary outcome measure. For PreCardio, this is, for instance, systolic blood pressure. Kelley *et al *found a mean systolic blood pressure of 125 mm/Hg (SD 14 mm/Hg)[42]. The sample size calculation was performed with Nquery Advisor 4.0^®^. A two group t-test with a 0,05 two-sided significance level will have 82% power to detect the difference between a Group 1 mean of 120 mm/Hg and a Group 2 mean of 125 mm/Hg, a difference in means of -5 mm/Hg, assuming that the common standard deviation is 14 mm/Hg, when the sample sizes in the two groups are 200 and 100, respectively (a total sample size of 300). Other outcome measures were also used to determine the necessary sample size. A recent study about the effect of a computer-tailored intervention to reduce fat intake included at post-test a mean fat intake of 85 grams/day (SD 34.5 grams/day) [43]. A two group t-test with a 0,050 two-sided significance level will have 80% power to detect the difference between a Group 1 mean of 85 grams/day and a Group 2 mean of 97 grams/day, a difference in means of -12 grams/day assuming that the common standard deviation is 34.5 grams/day, when the sample sizes in the two groups are 200 and 100, respectively (a total sample size of 300). Another study evaluating a website-delivered computer-tailored intervention for increasing physical activity increased physical activity with a mean of 77 minutes in the intervention group [44]. In this study the total moderate- and vigorous-intensity physical activity was chosen as an outcome measure. This measure can be used to determine the necessary sample size to detect a difference in means in the present study. At follow up this measure had a mean of 363 minutes (SD 323) for the intervention group and 241 minutes (SD 269) for the control group [43]. A two group t-test with a 0,05 two-sided significance level will have 86% power to detect the difference between a Group 1 mean of 363 minutes and a Group 2 mean of 241 minutes, a difference in means of 122 minutes, assuming that the common standard deviation is 323 minutes, when the sample sizes in the two groups are 200 and 100, respectively (a total sample size of 300).

A linear regression model will be employed to assess the effects of the prevention programme on change in overall cardiovascular risk from baseline to 3 year follow-up.

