### Randomization

The study participants were randomized using a nonstratified randomization technique with a known probability. Each participant had a 67% chance to be allocated to the intervention group. The randomization was performed by an independent person. The names of the participants were written on papers that were put in sealed envelopes. Next, the envelopes were randomly assigned by hand to two baskets for the intervention and the control group, respectively, with a ratio of 2/1.

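### The t-test of outcome means ignores the baseline values of the GP-measured continuous outcomes; it is valid, but adjusting for baseline would give more power from the same participants

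*Protocol article*

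**What the plan says.** The protocol article, under Analysis and power, fixes the comparison in one sentence: "A t-test will be used to compare the means of the outcome measures from the intervention and the control group". It names no covariate and no time point. The sample size rests on the same test. For systolic blood pressure, "A two group t-test with a 0,05 two-sided significance level will have 82% power" to detect "a difference in means of -5 mm/Hg, assuming that the common standard deviation is 14 mm/Hg", with 200 and 100 participants. The fat-intake and physical-activity calculations have the same form.

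Overall risk is handled differently: "A linear regression model will be employed to assess the effects of the prevention programme on change in overall cardiovascular risk" between baseline and three years. Covariates are not listed.

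Table 1 (Study measurements) schedules BMI, blood pressure, cholesterol and HbA1c with the GP at 0, 12, 24 and 36 months for everyone. The Design section says that the medical data of the first consultation are gathered before the risk is determined. The website questionnaire that supplies the behavioural baseline opens only after that consultation, at which the intervention group receives tailored feedback.

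On allocation, the Randomization section says "The study participants were randomized using a nonstratified randomization technique with a known probability", using "two baskets for the intervention and the control group, respectively, with a ratio of 2/1".

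**The concern.** A participant's blood pressure, cholesterol, HbA1c or BMI at entry usually predicts part of the same measurement three years later. A t-test of follow-up means leaves that predictable part in the error term, so confidence intervals are wider than the data require. It also lets any chance difference between the arms at baseline pass into the estimate in proportion to the correlation. Allocation is not stratified, so nothing in the design balances these values beyond chance.

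What is at stake is precision, not validity. The article also treats baseline in two ways, ignoring it for the individual risk factors and building it into the outcome for overall risk, without giving a reason for the difference.

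**Working it through.** **Inputs.** From Analysis and power: difference 5 mmHg (120 against 125), common SD 14 mmHg, two-sided 0.05, groups of 200 and 100. The SD comes from a cited study's mean blood pressure of 125 mmHg, so it is a between-person SD, not an SD of change or a residual SD. The correlation r between baseline and 36-month values is not in the article. It is assumed here and varied from 0.3 to 0.7.

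**Step 1: reproduce the stated power.** The standard error of the difference is 14 × √(1/200 + 1/100) = 14 × 0.1225 = 1.715 mmHg. The noncentrality is 5/1.715 = 2.92. The noncentral t with 298 degrees of freedom gives 82.8% (normal approximation 83.0%), against 82% stated. The same method gives 80.8% for fat intake (80% stated) and 86.7% for physical activity (86% stated). The article's power figures are therefore sound for the test it names.

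**Step 2: adjust for baseline.** In a linear model of the follow-up value on arm and baseline, the residual SD is 14 × √(1 − r²), with 297 degrees of freedom. The last column, 300/(1 − r²), is the total number that an unadjusted t-test would need for the same precision.

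| Assumed r | Residual SD (mmHg) | Standard error (mmHg) | 5 / standard error | Power | Equivalent unadjusted total |
|---|---|---|---|---|---|
| none (t-test) | 14.00 | 1.715 | 2.92 | 82.8% | 300 |
| 0.3 | 13.36 | 1.636 | 3.06 | 86% | 330 |
| 0.5 | 12.12 | 1.485 | 3.37 | 91.9% | 400 |
| 0.6 | 11.20 | 1.372 | 3.65 | 95.3% | 469 |
| 0.7 | 10.00 | 1.224 | 4.08 | 98.3% | 588 |

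**Step 3: chance baseline difference.** With the same SD at baseline, the difference between arms at entry also has a standard error of 1.715 mmHg, so a 95% range of about ±3.4 mmHg (1.96 × 1.715). The t-test estimate carries r times that difference. At r = 0.5, a baseline gap of 3.4 mmHg moves the estimate by 1.7 mmHg, about a third of the 5 mmHg target. The t-test's standard error already allows for this on average; the adjusted model removes it.

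**Step 4: the regression on change.** Write Y for the 36-month risk and B for baseline risk. If B is a covariate, Y − B = a + τ·arm + γ·B is the same model as Y = a + τ·arm + (γ + 1)·B, and τ is identical. Naming baseline risk as a covariate is therefore enough to make that analysis a baseline-adjusted one.

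**Step 5: which baselines can be used.** An adjusting value should not itself be affected by the intervention. The GP measurements meet this on the article's own sequence, because they precede the risk result and the feedback. The website questionnaire does not: the intervention group has already had tailored feedback at the consultation.

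**The case against.** The strongest reply is that nothing here is an error. A two-group t-test in a randomised trial is unbiased, holds its significance level, and has a standard error that already reflects chance imbalance. The stated 82% is correct and exceeds 80%, and 350 are to be enrolled for 300 in the calculation. Covariates are often left to an analysis plan, and the sentence stands in a paragraph about power. Most of this stands, and it limits the point to efficiency. But the article does not leave the method open: it says which test will be used, and a better one is available on the same data.

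Some stronger readings are tempting but not supported:

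- A reader might infer that power would rise to a single high figure such as 92–95%. That needs r of about 0.50 to 0.59, and the article gives no correlation. Over three years, with GPs starting treatment, r may be lower; at 0.3 the gain is about 3 points.
- A reader might infer that every outcome has a baseline to adjust for. Cardiovascular events and costs have none, and autonomous motivation and intention are not in Table 1. The primary aims on a 10% reduction are proportions already defined against baseline.
- A reader might infer that overall risk will be analysed as a bare change score, which loses to a t-test when r is below 0.5. The article neither states nor excludes a baseline covariate there, and it plans no change-score analysis of blood pressure.
- A reader might infer that adjustment is free throughout. For the website outcomes it would mean adjusting for a value taken after feedback, which could remove part of an early effect.

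**Conclusion.** The point holds for the GP-measured continuous primary outcomes: systolic and diastolic blood pressure, total cholesterol, HbA1c and BMI. The planned t-test is valid but less precise than the scheduled data allow. For systolic blood pressure, power goes from about 83% to between 86% and 98% for assumed correlations of 0.3 to 0.7, equivalent to about 330 to 588 participants analysed without adjustment instead of 300.

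The direction does not hinge on one chosen correlation, since adjustment gave more power at every value checked from 0.2 upward (84.3% at 0.2). The size does depend on it. The calculation also assumes the article's SD of 14 mmHg, a common residual variance and the 36-month value as the outcome. The gain was not computed for the other GP-measured outcomes, for which the article gives no effect size or SD.

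**What to change.** Under Analysis and power:

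- For the GP-measured continuous outcomes, replace the t-test with a linear model of the 36-month value on arm and the participant's own 0-month value of that outcome. A mixed model over the 12-, 24- and 36-month visits, with baseline adjustment and the 36-month contrast as the estimate, serves equally well.
- In the sentence on overall risk, state that baseline risk is a covariate.
- The sample size may stay as it is. If a gain in power is quoted, give it as a range over assumed correlations.

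These are wording changes. They need no extra participants, visits or measurements.

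For physical activity, fat intake, and fruit and vegetable intake, adjust for baseline only if the questionnaire is moved ahead of the first consultation. That is a small change to the collection schedule. If it is not made, do not adjust for the questionnaire values as now timed.

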## Methods/Design

### Study population

PreCardio is a randomized controlled trial. Approval was obtained from the ethics committee of the University Hasselt. A total of 350 subjects will be included in the study with a follow-up of 3 years. The inclusion criteria are age between 25–65 and insured by the Onderlinge Ziekenkas, insuring for guaranteed income in case of illness for self-employed. All study participants need to sign an informed consent and have access to the internet. Other eligitability criteria are not included.

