#### Primary aims

1. To examine the effects of medical and behavioural interventions on medical parameters such as systolic blood pressure, diastolic blood pressure, total blood cholesterol level, blood glucose level (HbA1c), overweight and obesity, BMI.

2. To examine the effects of medical and behavioural interventions on health related behaviour such as physical activity; fat; fruit and vegetable intake; and smoking behaviour.

3. To examine the effects of medical and behavioural interventions on overall cardiovascular risk mediated by changes in medical and/or behavioural risk factors.

4. To determine the proportion study participants with a 10% reduction in systolic blood pressure with participants with hypertension

5. To determine the proportion study participants with a 10% reduction in diastolic blood pressure with participants with hypertension

6. To determine the proportion study participants with a 10% reduction in total cholesterol with patients with hypercholesterol

7. To determine the proportion study participants with a 10% reduction in HB1Ac with initial HB1Ac >7% (high risk)?

8. To determine the proportion study participants with a 10% reduction in weight with initial BMI >25 kg/m^2^?

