### Interventions

#### Minimal intervention

##### Medical prevention consultation

The interventions targeted on medical parameters include a first medical prevention consultation with the GP. In this medical prevention consultation the cardiovascular risk (risk on having a heart attack in the next 10 years) will be calculated using a new computer programme. This computer programme is called "Electronic Prevention Record" (EPR). Innovative about the EPR is its connection to "Electronic Medical Record" (EMR). The EMR is also a computer programme, a record about the medical history and treatment provided to the patient. In the province of Limburg, the setting for the PreCardio-study, 75% of the GPs use an EMR[36]. In Belgium, 70% of the GPs use an EMR [37]. In Belgium there are 17 different providers of EMRs. The EPR generates, after a limited input (thanks to the connection to the EMR), the cardiovascular risk, the therapeutic goals (targeted on medical parameters and behaviour change) and a target date for the next follow-up consultation. This date is dependent on the determined cardiovascular risk. During these medical prevention consultations medical practice will be performed: measurement (e.g. blood pressure) and installation of treatment to influence medical parameters. Supplementary, the GP performs stage of change assessment (Table 2) using the EPR. The GP asks for PA and diet which statement fits the participant's situation best. If it is a smoker, the stage of change for quitting smoking is assessed as well. The stage of change assessment is for the control group not followed by tailored feedback for behaviour change.

All data collected at the medical prevention consultation are stored in the EPR that is connected to the EMR (Fig 4). Therapeutic goals in line with cardiovascular risk are determined. These goals, together with the data provided by the study participant are electronically sent to the study office by a secured connection. The information from the intervention group is closely examined and the participants of the intervention group will receive a reminder from the study office when it is time to plan their next medical prevention consultation.

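### Smoking is a primary outcome in a sample not selected on smoking, but the only comparison stated for it is a two-group t-test of means that takes no account of baseline smoking

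*Protocol article*

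**What the plan says.** All places are in the protocol article.

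- **Primary aims, aim 2** covers "health related behaviour such as physical activity; fat; fruit and vegetable intake; and smoking behaviour".
- **Study population** sets age, insurer, consent and internet access as the conditions for entry, and adds: "Other eligitability criteria are not included".
- **Medical prevention consultation** (minimal intervention) shows that non-smokers are expected in the sample: "If it is a smoker, the stage of change for quitting smoking is assessed as well". The same step appears under the maximal intervention.
- **Analysis and power** gives the comparison: "A t-test will be used to compare the means of the outcome measures from the intervention and the control group". The only other model is for a different outcome: "A linear regression model will be employed to assess the effects of the prevention programme on change in overall cardiovascular risk".
- **Primary aims, aims 4 to 8** look at responders among people who have the risk factor, for example: "To determine the proportion study participants with a 10% reduction in systolic blood pressure with participants with hypertension". Smoking has no such aim.

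The article gives no smoking prevalence, quit rate or power figure for smoking. It does not say whether smoking is scored as status, amount or cessation, or whether the follow-up value or the change is compared.

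**The concern.** A participant who does not smoke at baseline cannot quit. If smoking at follow-up is compared across all participants, a cessation effect is multiplied by the proportion who smoked at entry. The chance difference between arms in baseline smoking stays in the comparison as noise. A t-test of means on such an outcome is valid but can be weak. A null result on a primary aim could then be read as absence of effect when the comparison had little chance of showing one. The data needed for a sharper comparison are already collected in both arms.

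**Working it through.** **1. The plan's own figure.** Inputs from Analysis and power: difference 5 mmHg, SD 14 mmHg, groups of 200 and 100, two-sided 5%.

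- Standard error = 14 × √(1/200 + 1/100) = 1.715.
- Standardised difference = 5 / 1.715 = 2.916.
- Power ≈ Φ(2.916 − 1.96) = 83%; the exact noncentral t gives 82.8%. The article states: "A two group t-test with a 0,05 two-sided significance level will have 82% power".

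The fat intake and physical activity figures also reproduce, at 80.8% and 86.7% against 80% and 86% stated. The sizing is sound for those outcomes; none of them is smoking.

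**2. Assumptions for smoking.** Group sizes of 200 and 100 come from the article. The rest is assumed: baseline smoking 15 to 30%, quit rates of 25% (intervention) and 10% (control), no uptake and no relapse.

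**3. One setting by formula, 25% smokers.** Power = Φ[(δ − 1.96 × SE₀) / SE₁], where SE₀ uses the pooled proportion and SE₁ the separate proportions.

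- *Follow-up status, everyone.* Proportions smoking are 0.25 × 0.90 = 0.225 and 0.25 × 0.75 = 0.1875, so δ = 0.0375. Pooled proportion 0.20; SE₀ = √(0.16 × 0.015) = 0.0490; SE₁ = 0.0501. Power = Φ(−1.17) = 12%.
- *Abstinence among baseline smokers (25 and 50 people).* δ = 0.15. Pooled proportion 0.20; SE₀ = √(0.16 × 0.06) = 0.0980; SE₁ = 0.0857. Power = Φ(−0.49) = 31%.
- *Change from baseline, everyone (non-smokers count as zero).* Proportions 0.025 and 0.0625, so δ = 0.0375. Pooled proportion 0.05; SE₀ = √(0.0475 × 0.015) = 0.0267; SE₁ = 0.0232. Power = Φ(−0.64) = 26%.

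The first and third analyses have the same δ. They differ in noise: status carries the chance imbalance in baseline smoking, with SD √(0.25 × 0.75 × 0.015) = 5.3 percentage points against an effect of 3.75 points. Change removes it.

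**4. Simulated power over the range** (independent runs agree to within about two points):

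| Baseline smokers | Status, everyone, t-test | Change, everyone, t-test | Smokers only, Pearson | Smokers only, Fisher |
|---|---|---|---|---|
| 15% | 9% | 13% | 18% | 13% |
| 20% | 11% | 20% | 26% | 21% |
| 25% | 12% | 26% | 32% | 26% |
| 30% | 14% | 31% | 38% | 32% |

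The relative loss from comparing status in everyone runs from 1 − 9/18 = 50% to 1 − 14/38 = 63% against Pearson, and from 1 − 9/13 = 31% to 1 − 14/32 = 56% against Fisher. For change, it runs from 1 − 31/38 = 18% to 1 − 13/18 = 28% against Pearson and is negligible against Fisher. With quit rates of 30% against 10% and 25% smokers, power is about 18% (status), 40% (change) and 50% (Pearson).

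**5. Type I error.** With equal quit rates in the arms, the whole-group test of status rejects in about 5% of simulated trials (4.3 to 5.8% across settings).

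**The case against.** The strongest reply is that the t-test sentence stands in a power paragraph whose worked examples are all continuous. Aims 4 to 8 are proportions in subgroups, which a comparison of whole-group means does not naturally cover, so the sentence may not be the whole plan. A fuller protocol or analysis plan may define the smoking outcome. This limits the weight of the point but does not remove it: the article names a method for the outcome measures in general, smoking is one of them, and the method suits it poorly.

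A second reply is that the t-test in everyone does not itself cause the loss. This stands. A t-test of change performs about as well as Fisher's test among smokers. The follow-up and post-test means used for the fat and activity power examples suggest that follow-up values are compared, but they do not settle it for smoking.

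Third, with 15 to 30 control smokers and a 10% quit rate, only 1.5 to 3 control quitters are expected. An exact test is then the fair benchmark, and the gain over whole-group status is about 1.4-fold (13/9) to 2.3-fold (32/14). This also stands.

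Fourth, the aim is smoking behaviour, not cessation alone, and the website uses relapse-prevention techniques. Restricting to smokers narrows the question, and the calculation's assumption of no uptake or relapse leaves out anything that a whole-group comparison could gain there. Relapse and uptake therefore need their own report.

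**Conclusion.** The point holds as a conditional one. A primary outcome is left with a generic whole-group comparison of means, without restriction to or adjustment for baseline smoking. If that means follow-up status in everyone, power is about 9 to 14%, against 18 to 38% (Pearson) or 13 to 32% (Fisher) among baseline smokers, under the assumed prevalence and quit rates.

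Two stronger readings are tempting and not supported. A reader might infer that the plan as written forfeits half to two-thirds of the attainable power. That needs the status reading, Pearson's test as benchmark, and a prevalence and quit rates that the article does not give; even a non-smoking majority is an assumption. A reader might also infer that chance imbalance in baseline smoking could produce a spurious effect more often than the nominal level allows. It does not: allocation is randomised, the test keeps its 5% level, and imbalance only adds noise.

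The remedy leaves power for smoking modest. This is a cheap improvement, not a threat to the trial's validity.

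**What to change.** State in the analysis section:

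- The main smoking outcome is abstinence at follow-up among participants recorded as smokers at the first GP consultation. That record is preferable to the website baseline questionnaire, which opens only after the consultation at which the intervention group receives tailored feedback.
- Arms are compared by risk difference with a confidence interval and a test for proportions, exact where counts are small. Alternatively, with the same intent, follow-up smoking is analysed in everyone with adjustment for baseline smoking.
- Relapse among former smokers and uptake among other non-smokers are reported separately.
- The t-test is kept for continuous outcomes.

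The cost is wording only: smoking is already measured in both arms, and no visit or participant is added. The downside is that the main smoking estimate then applies to baseline smokers only, with a smaller denominator.
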